#### Outcomes

##### Primary outcomes

Adherence will be assessed through retention and attendance rates. The retention rate will be analyzed by the percentage of participants completing all sessions of the intervention (16 in total) as well as the percentage of participants present in each step of study until the last evaluation at the follow-up period. Attendance rate will be analyzed by the mean of presences of the participants divided by the number of sessions offered during the 8-week intervention, multiplied by 100. The recruitment rate will be expressed by percentage and analyzed by the number of eligible individuals recruited per month. We will consider a recruitment and retained rate of > 80% as feasible to conduct a future randomized control trial. Safety will be reported by the number of adverse events. Adverse events were defined as exercise intolerance, injuries, or falls during the intervention [39], considering < 5% of occurrence of adverse as acceptable to conduct a future randomized control trial. The acceptability of the protocol by the participants will be better elucidated by the qualitative analysis in a general way (Fig. 4).

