**Method:**

A 12-week pilot for a randomized clinical trial will assess the feasibility and preliminary effectiveness of the EMPOWER-PD and make comparisons with conventional physical therapy (CPh). Both protocols consist of mobility and locomotion training, and aim at improving motor and non-motor symptoms through different approaches. The EMPOWER-PD aims to provide a source of motivation and empowerment of health through the self-knowledge of the individual’s abilities and limitations, in a protocol that addresses individual preferences. The CPh is based only on physiotherapist decisions, not addressing the individual’s preferences or motivation/empowerment. The target recruitment will be 24 PD individuals, between stages I and III of Hoehn and Yahr (HY), who will be recruited from Brazilian Parkinson’s disease Rehabilitation Initiative (BPaRkI) with allocation ratio 1:1. A computerized block randomization procedure will be implemented by a blinded researcher with the participants blinded to group assignment. The sessions will be conducted in a group setting, twice a week, during 60 min for 8 weeks, followed by 4 weeks of follow-up. The primary outcomes will be the feasibility data (adherence, recruitment rate, and safety). The secondary outcomes will assess the preliminary efficacy on qualitative assessment about individual’s motivation/empowerment and quantitative motor outcomes (Timed Up and Go and Dynamic Gait Index) and non-motor symptoms (6-min walk test and Fatigue Severity Scale). The recommendation to have 6–12 participants per group will be adopted based on the qualitative analysis to the sample size.

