#### Sample size

The primary outcome of this pilot for a randomized clinical trial will be the feasibility (adherence, recruitment rates and safety). As in feasibility studies a formal sample size calculation is not required [30], we estimated the number of participants based on qualitative analysis. We will adopt the recruitment of 6–12 participants per group as a recommended for qualitative studies, being adopted the major value (*n* = 12 per group) [31]. Accordingly, we will use the criteria of sampling saturation that means “collecting data until no new information is obtained” [32].

In relation to the quantitative variables, the present study is not intended to be fully powered for detection of statistically significant effects, but it will enable a sample size calculation related to the quantitative variables for a future randomized trial [33]. For that, we plan to select the sample size based on reasonable precision of estimates of standard deviation of quantitative measures which have shown sensitivity in this feasibility study.

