#### Interventions groups

The treatment sessions will be performed in group, twice a week, for 8 weeks, completing 16 sessions followed by a 4-week follow-up period. Before and after each session, blood pressure will be measured. The exercise intensity will be monitored every 5 min by an oximeter and the modified Borg scale [37] will be applied to verify the perception of effort in both groups by two physical educators for group. However, in the CPh group, the exercise intensity will be controlled between 55% and 85% of maximum heart rate (HR_max_) [2], according to the Karvonen’s formula. Each individual value will be calculated previously the interventions and vebaly stimulated during the session by the physical educator to keep up with the recommended HR values, increasing or slow walking speed. It is important to note that the intensity of the EMPOWER-PD protocol will be self-controlled according to the self-perception of effort of each one. The activities will be carried out during the “on” phase of the medication lasting 1 h, divided into 10 min of heating, 40 min of main part, and 10 min of back to calm [38] in an outpatient space.

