### Procedures

The baseline assessment will be conducted once participants have given informed consent. All interviews/scales will be applied individually in a private setting by a blinded researcher, and all participants will receive an identification number. All evaluation will be performed in the afternoon, with individuals on the “on” phase of the medication. Demographics and eligibility criteria information will be collected at the baseline step. From there, the volunteers eligible in the inclusion criteria will be randomized into one of the two groups (EMPOWER-PD group and conventional physical therapy group) by a second researcher not involved in other steps.

Participants allocated to both groups will receive 8 weeks of intervention that will occur at the same time in different places to minimize individuals’ awareness of the differences between interventions. Then, the participants will be assessed at post-intervention, always by the same physiotherapist research, followed by a follow-up period of 4 weeks. The main objective of this stage of the study is to verify if the intervention would be a source of motivation/empowerment of health for a more proactive life, and in this way, decrease the dependency of professional supervision to remain active. For this, the participant will remain 4 weeks without any guidance from the therapist. After this, they will be contacted by phone to schedule the final evaluation, which will be performed on all outcome variables of the others stages of the study. Participants who drop out of the study will also be contacted by phone for the final evaluation.

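### Retention is defined by two non-equivalent percentages under one >80% progression rule, and the all-16-sessions version can fail a very well attended trial

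*Protocol article*

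**What the plan says.** All of this is in the protocol article. Under Primary outcomes, adherence is assessed through a retention rate and an attendance rate. Retention has two components:

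- Session completion: "The retention rate will be analyzed by the percentage of participants completing all sessions of the intervention (16 in total".
- Presence at assessments: "as well as the percentage of participants present in each step of study until the last evaluation at the follow-up period".

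Attendance is a separate measure with no threshold: "Attendance rate will be analyzed by the mean of presences of the participants divided by the number of sessions offered during the 8-week intervention".

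The progression rule follows: "We will consider a recruitment and retained rate of > 80% as feasible to conduct a future randomized control trial". It does not name the retention component, the time point, or whether it applies per arm or to the whole sample.

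Interventions groups gives the programme as "twice a week, for 8 weeks, completing 16 sessions followed by a 4-week follow-up period". The abstract sets the size: "The target recruitment will be 24 PD individuals". Procedures adds: "Participants who drop out of the study will also be contacted by phone for the final evaluation".

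**The concern.** Retention is part of the primary outcome and a stated condition for going on to a definitive trial. It also bears on the Background hypothesis that EMPOWER-PD gives higher adherence, since adherence is measured through retention and attendance.

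The two components measure different things. The first is perfect attendance: one absence in 16 makes a participant not retained, and no lower number of sessions counts as completion. The second is presence at assessment. With one threshold over both, whoever reads the results can choose the verdict after seeing the data, and one choice can call a programme unfeasible because of a few scattered absences.

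A smaller problem sits in the second component. People who left the study are called back for the final evaluation, so someone who abandoned the intervention can count as present at the last step.

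**Working it through.** **Inputs.** Sessions: 2 per week × 8 weeks = 16, which matches the stated 16. Participants: 2 × 12 = 24, which matches the stated target. The article gives no expected attendance and no within-person correlation of absences, so both are assumptions below.

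**What more than 80% requires.** 0.80 × 24 = 19.2, so at least 20/24 (83.3%); 19/24 = 79.2% fails. If read per arm, 0.80 × 12 = 9.6, so at least 10/12 (83.3%); 9/12 = 75% fails.

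**Examples that need no probability model.** Everyone is assessed at every step, so step presence is 24/24 (or 12/12) = 100%.

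| Pattern of absence | Attendance | All 16 completed |
|---|---|---|
| 5 of 24 miss one session each | (384 − 5)/384 = 98.7% | 19/24 = 79.2%, fails |
| The same 5 absences among 4 people | 379/384 = 98.7% | 20/24 = 83.3%, passes |
| All 24 miss one session each | 15/16 = 93.75% | 0/24 = 0%, fails |
| One arm: 3 of 12 miss one session each | (192 − 3)/192 = 98.4% | 9/12 = 75%, fails if read per arm |

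**Independent absences.** With per-session attendance p, the chance of completing all 16 is q = p^16, and the chance of meeting the rule is P(X ≥ 20) for X ~ Binomial(24, q).

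| p | q = p^16 | P(at least 20/24) |
|---|---|---|
| 0.90 | 18.5% | <0.0001 |
| 0.95 | 44.0% | 0.0001 |
| 0.97 | 61.4% | 0.019 |
| 0.98 | 72.4% | 0.17 |
| 0.99 | 85.1% | 0.72 |
| 0.995 | 92.3% | 0.97 |

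Expected completion reaches 80% at p = 0.80^(1/16) = 0.986.

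**Clustered absences.** Some people miss more sessions than others. A beta-binomial model with mean attendance m and intraclass correlation ρ has a = m(1 − ρ)/ρ and b = (1 − m)(1 − ρ)/ρ. Then q = Γ(a + 16)Γ(a + b) / [Γ(a)Γ(a + b + 16)].

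| m | ρ | q | P(at least 20/24) |
|---|---|---|---|
| 0.95 | 0.1 | 61.6% | 0.02 |
| 0.95 | 0.2 | 70.6% | 0.12 |
| 0.95 | 0.3 | 76.5% | 0.31 |
| 0.95 | 0.5 | 84.3% | 0.68 |
| 0.98 | 0.1 | 82.6% | 0.59 |
| 0.98 | 0.3 | 89.9% | 0.91 |

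At 95% attendance the all-16 component more often fails than passes up to ρ = 0.3, and the balance turns by ρ = 0.5. At 98% with ρ of 0.1 or more, passing is the likelier result.

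**Recalled drop-outs.** Suppose 5 of 24 withdraw before week 8, miss that assessment, and all return at week 12. Step presence is 19/24 = 79.2% at week 8 and 24/24 = 100% at week 12. The recall inflates only the last step.

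**The case against.** A reader who stops at the first half of the retention sentence might infer that only participants with all 16 sessions are counted, and that a nearly perfectly attended trial would therefore be declared unfeasible. The article does not support that. The same sentence adds presence at each step, and the rule does not say that session completion governs. The phrase "retained rate" fits step presence at least as well, particularly as session exposure has its own measure, the attendance rate. Read on step presence, a fully assessed trial scores 24/24.

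Even on the strict reading, failure is not assured. At 99% attendance with independent absences the rule is met with probability 0.72. The five-absence example fails only when the absences fall on five different people. The near-zero pass probabilities rest on independence, which nothing in the article supports. Recall of drop-outs cannot hide a loss at week 8.

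The remaining defence is one of proportion. This is a 24-person pilot not powered for effects, all the percentages are to be reported, and the strict reading errs towards caution. The absence of an attendance threshold is a choice and not an error. These arguments lower the severity. They do not remove the defect. Nor is this a detail that an article can be expected to leave to a fuller document, because the article itself states the rule and sets it over two quantities that can disagree.

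**Conclusion.** The point stands in limited form and should be fixed. One threshold of more than 80% covers two retention percentages that are not equivalent, with no statement of which decides or whether both must pass. If all-16 completion decides, alone or jointly, a trial with 98.7% attendance and every participant assessed can fail at 79.2%. That example is plain arithmetic on the stated 24 participants and 16 sessions.

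How likely such a failure is depends on assumptions that the article does not supply. At 95% attendance it is close to certain with independent absences and still more likely than not with intraclass correlation up to 0.3. At 99% or more, passing is more likely than failing. No estimate of treatment effect is affected; what is at risk is the feasibility verdict.

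**What to change.** Reword the primary outcome and the progression rule:

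- **Progression rule.** Apply the threshold of more than 80% to the proportion of randomised participants who have not withdrawn and are assessed at week 8 and at week 12: at least 20/24 overall. Report the figure by arm as well, without making the arm figure a second hurdle.
- **Precision.** Give exact (Clopper-Pearson) 95% intervals. A result of 20/24 has an interval of 63% to 95%, and 10/12 has 52% to 98%, so a bare pass says little about the true rate.
- **Session completion.** Report completion of all 16 sessions descriptively, outside the rule.
- **Exposure.** Report the attendance rate already defined, with all randomised participants × 16 sessions (24 × 16 = 384) as denominator, so that drop-outs stay in it.
- **Recalled drop-outs.** Count them as assessed at the final evaluation, not as retained in the intervention.

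The cost is a few sentences; the planned attendance and assessment records suffice. The choice should be fixed before the retention data are seen. Trial status gives October 2018 as the end date. If the data are already known, set both percentages against 80% and say that the deciding one was named afterwards.

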Based on all information above, this study presents the EMPOWER-PD protocol, a physical therapy approach based on the individual preferences. As a new intervention protocol, it is necessary to verify it feasibility when applied to the target population. This study presents the design of the feasibility randomized controlled trial that aims to(i)Investigate the feasibility of the EMPOWER-PD protocol through adherence rate, recruitment rate, and safety.(ii)Compare the preliminary effectiveness of the EMPOWER-PD with the conventional physical therapy through qualitative analysis of motivation, empowerment of health, followed by the analysis of the dependency of professional supervision by individuals to remain active in the post follow-up period.(iii)Compare the preliminary effectiveness of the EMPOWER-PD in motor and non-motor symptoms (functional mobility, gait, fatigue, aerobic capacity/endurance) with the conventional physical therapy through quantitative analysis of estimates of 95% confident interval.

We hypothesize that the EMPOWER-PD will lead to higher adherence and safety when compared with conventional physical therapy. Concerning motivation, health empowerment and dependency of professional supervision by individuals to remain active in the post follow-up period, we hypothesize that the EMPOWER-PD will be associated with better outcomes in preliminary effectiveness than the conventional physical therapy. For the motor and non-motor symptoms, we hypothesize that the EMPOWER-PD will be associated with similar preliminary effectiveness to the conventional physical therapy.

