### Data management and analysis

For the feasibility analysis, the results will be expressed as percentage and numbers referring to adherence, recruitment rates, and safety, respectively. After qualitative data collection, two authors will perform the total transcription of the audios and notes line-by-line. Then, two authors will start the codification of the *corpus.* After transcription, the corpus will be codified in numbers and their respective groups (e.g., # ID1emp, # ID5cph) by a blinded third researcher, for the later analysis by a fourth researcher. Codes will then be consolidated into categories after an extensive exploration of the material and interpretation of the data obtained according to thematic analysis of the content. From this, entire research team will discuss to formulate inferences.

To verify the preliminary effectiveness regarding quantitative outcomes, the descriptive analysis will be performed with frequency, central tendency, and variability (mean and standard deviation or median and interquartile interval) in the statistical program SPSS 20.0 for Windows (IBM-USA). All results of the preliminary efficacy of the feasibility trial will be described as estimates of 95% confidence interval. An intention-to-treat analysis will be done with participants including who eventually will be missed in any part of the study.

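### Safety is planned as a bare number of adverse events although attendance is expected to be higher with EMPOWER-PD, so the count needs an exposure-adjusted rate by arm beside it

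*Protocol article*

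**What the plan says.** Four statements in the protocol article bear on this.

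- **Hypothesis (Background, after the aims).** "We hypothesize that the EMPOWER-PD will lead to higher adherence and safety when compared with conventional physical therapy". One sentence predicts a between-arm difference in both quantities.
- **Adherence (Primary outcomes).** "Adherence will be assessed through retention and attendance rates". Attendance is defined from sessions: "Attendance rate will be analyzed by the mean of presences of the participants divided by the number of sessions offered during the 8-week intervention".
- **Safety (Primary outcomes).** "Safety will be reported by the number of adverse events". The time window is given with the definition: "Adverse events were defined as exercise intolerance, injuries, or falls during the intervention". The only proportion attached to safety is the criterion for proceeding, "considering < 5% of occurrence of adverse as acceptable to conduct a future randomized control trial", which names no denominator.
- **Analysis (Data management and analysis).** For feasibility, "the results will be expressed as percentage and numbers referring to adherence, recruitment rates, and safety, respectively". Read with its last word, percentages go to adherence and recruitment, and numbers go to safety.

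Nowhere does the article relate the number of events to sessions attended.

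**The concern.** Exercise intolerance, and injuries or falls on the circuit, can happen only to people who are present. For such events an arm's expected count is the product of per-session risk and sessions attended. The trial expects the second factor to be larger with EMPOWER-PD. The two halves of the hypothesis therefore pull against each other: the better the programme keeps people attending, the more chances there are to record an event in that arm. Conversely, an arm that people stop attending can look safer because fewer people are there to have an event.

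Safety is one of the primary feasibility outcomes and no formal test is described, so readers will judge the safety hypothesis from the reported figures. A count shown alone mixes risk with attendance. A larger sample would reduce the noise but not this systematic part.

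**Working it through.** The article gives no expected event rate or attendance for safety, so there is no planned figure to reproduce. The check is exposure arithmetic over a range of assumptions.

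**Inputs from the article**
- "The target recruitment will be 24 PD individuals", allocated 1:1, so 12 per arm (Abstract; Sample size; Randomization).
- 16 sessions offered per participant (Interventions groups).
- Person-sessions offered per arm: 12 × 16 = 192.

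**Assumptions (not in the article)**
- Attendance in each arm, per-session risk, and the per-session risk ratio RR (EMPOWER-PD to CPh).
- Events arise in attended sessions, and counts are Poisson.

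**Formulas**
- Expected count = 192 × attendance × per-session risk.
- Ratio of expected counts = (EMPOWER-PD attendance ÷ CPh attendance) × RR.
- In expectation the count points the wrong way on per-session risk when RR lies between CPh attendance ÷ EMPOWER-PD attendance and 1.

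**Step 1: equal per-session risk (RR = 1)**

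| Assumed attendance, EMPOWER-PD v CPh | Expected count ratio | RR range in which expected counts reverse |
|---|---|---|
| 90% v 80% | 0.90/0.80 = 1.125 | 0.89 to 1 |
| 95% v 75% | 0.95/0.75 = 1.267 | 0.79 to 1 |
| 95% v 60% | 0.95/0.60 = 1.583 | 0.63 to 1 |

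**Step 2: a modest true advantage.** At 95% v 75% with RR = 0.85, the ratio is 0.85 × 1.267 = 1.077. The arm with the 15% lower per-session risk still has an expected count about 8% higher. At 90% v 80% the same RR gives 0.85 × 1.125 = 0.956, so the direction is right but the 15% advantage shrinks to about 4%.

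**Step 3: what a single trial would show.** At 95% v 75%, with equal per-session risk (difference of two Poisson counts):

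| Assumed per-session risk | Expected counts | EMPOWER-PD has more | Tie | EMPOWER-PD has fewer |
|---|---|---|---|---|
| 0.5% | 0.91 v 0.72 | 0.38 | 0.35 | 0.27 |
| 1% | 1.82 v 1.44 | 0.47 | 0.23 | 0.31 |
| 5% | 9.12 v 7.20 | 0.64 | 0.09 | 0.27 |

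With equal attendance the chances of more and of fewer would be the same in every row.

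**Step 4: chance alone.** With equal 85% attendance, 1% risk and RR = 0.85, EMPOWER-PD still shows more events with probability 0.33 and fewer with 0.43. At low event numbers noise is at least as important as the attendance effect.

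**Step 5: after adjustment.** Dividing each count by attended sessions cancels attendance. At equal per-session risk the ratio of expected rates is 1.00 at any attendance split.

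**Step 6: does the 5% criterion supply the denominator?** It could mean fewer than 0.05 × 12 = 0.6 events per arm by participant, 0.05 × 24 = 1.2 over both arms, or 0.05 × 192 = 9.6 per arm by session offered. It does not settle the exposure basis, and it is a criterion for a future trial rather than a contrast between arms.

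**The case against.** The case on the other side is substantial.

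- **No between-arm test on counts is planned.** Safety falls under the first aim, which investigates feasibility, whereas the second and third aims compare. A reader might infer that the plan formally compares safety by raw counts. It does not say so. The contrast comes from the hypothesis sentence and from general wording about making comparisons with CPh. This stands, and it limits the point to how the hypothesis is read.
- **A count per randomised participant is a legitimate measure.** With 1:1 allocation it answers what happens to people offered each programme, which fits the intention-to-treat statement. This also stands. The article does not say that higher safety means lower per-session risk, so making the rate the sole basis would impose a choice. It is a reason to show both.
- **The time window is ambiguous.** If events during the intervention include falls at home over the 8 weeks, attendance matters less for those events. This weakens the mechanism without removing it for exercise intolerance and circuit injuries or falls.
- **Reversal is not assured.** A reader might infer that the safety hypothesis will be answered with the wrong sign. That needs a true risk ratio inside the bands in step 1, and a large advantage would still show. The 5% per-session row implies about nine events among 12 people, which is high; the 1% row is the more cautious illustration.
- **A reader could divide by attendance.** That is possible, since attendance is reported too, but the article does not say that the safety hypothesis will be read that way. Fixing it beforehand avoids choosing the measure after the results are known.
- **Overlap with the undefined 5% denominator.** Defining occurrence per attended session and reporting it by arm would settle both matters, so they can be handled together.

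**Conclusion.** The point holds in a limited form. The article fixes safety as a number of events and, in the same hypothesis sentence, expects higher adherence and higher safety with EMPOWER-PD. As a measure of per-session risk, the raw count is biased against EMPOWER-PD by the attendance ratio whenever attendance is higher in that arm: about 13% at 90% v 80% and 27% at 95% v 75%. A modest advantage can be masked or, within the stated risk-ratio bands, reversed in expectation.

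This rests on assumed attendance and risk, and on events arising mainly in sessions. The documents do not support saying that a formal comparison is planned on counts, that reversal is likely in general, or that counts per randomised participant are invalid. With 12 per arm, neither the count nor the rate will settle the safety hypothesis. The rate removes the systematic part only. It is a reporting change worth making because it costs almost nothing.

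**What to change.** In Primary outcomes and in Data management and analysis, state that for each arm the report will give:

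1. the raw number of adverse events; and
2. adverse events per attended person-session, with attended sessions taken from the attendance record, and an exact Poisson 95% interval for each arm and for the rate ratio.

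Add that the safety hypothesis will be read with the rate beside the count, not from the count alone. State whether events outside sessions are included. If they are, tally them separately and keep them out of the per-session rate.

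**Cost.** One or two sentences. Presences are already needed for the attendance rate, so the denominator requires no new data; each event must be marked as inside or outside a session. The downside is width: with 2 v 2 events and equal exposure, the exact 95% interval for the rate ratio runs from about 0.07 to 14. That shows how little a trial of this size can say about relative safety, which a bare count would hide.

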##### Empower-PD

Before the intervention sessions, the physiotherapist responsible for applying the interventions will collect the preferences of each participant from an anamnesis with questions such as what is your routine on a weekday? and on the weekend?; what activity do you most enjoy doing in your routine?; what do you like to do in your free time?; do you practice any kind of art?; in what daily life activity can you perceive your body more?; and others if therapist judge necessary in their reality. With this information, the therapist can start to plan how to adapt the protocol to the participants, for example with music, materials used in leisure activities, group dynamics, musical instruments, materials used in their routine, among others.

All the participants recruited and enrolled to EMPOWER-PD protocol will be training in a mixed circuit, at the same time, involving walking in solo training in different contexts (crossing obstacles, reaching activities, circumventing obstacles, passing through narrow spaces, dual-functional-task walking) (Fig. 2). In addition, to sit and stand training and the pivot with progressions will be specific to each task. It will be applied from the main part of 40 min duration, being allowed pauses to rest according to the individual’s perception. The main part starts with all participants inside the circuit. Some individuals will be sitting and in the other side, the others will be standing. When the therapist or the participant said to start, all will move together to the next station. Each station will require different tasks that will progress every 2 weeks focused on their activities of daily living and in challenging exercises according to motor control principles. The circuits will include mounted steps, chairs at different heights and benches, cones, red, green and yellow signs, items of preferential use (gardening, musical instruments, cleaning), which are behind the “U” or pivot-floor marking. The interaction with the preferred items will be done when the participants are in the “U” or pivot, during the period that the whole group went to their positions. Detailed descriptions of the interventions and their progressions are presented in Table 1.

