**Fig. 3 Fig3:**
[figure not shown]
Conventional physical therapy protocol

The therapists will have free choice to use feedbacks, and their instructions will be more related to the execution of the exercise than to the stimulus of self-knowledge of the patient. In this way, the warm-ups will have active joint mobilization exercises, increasing the speed of movement progressively according to the therapist’s command to the group. In the “back to calm” stage, breathing exercises will be performed, starting from diaphragmatic exercises to sustained inspiration and inspiration in times with the association of the upper limbs.

The training will follow the same EMPOWER-PD base structure (mixed, varied, and in blocks), featuring walking in solo, sit-and-lift, and pivot training with specific progressions for each stage of the circuit and increasing the level of difficulty of the complete task by increasing the speed from the therapist’s command. All the participants recruited and enrolled to the CPh will be training at the same time as well as in the Empower-PD group. However, we will control the exercise intensity (55 to 85% of HR_max_, as described previously). The therapy will be in group but without doubles or trios. The materials used in this protocol are the same as the EMPOWER-PD with the addition of the timer to control the execution speed of the circuit in some stages of the CPh protocol. The description of the exercises and their progressions during each week are explained in Table 2.

**Table 2 Tab2:** Conventional physical therapy. 8-week physical therapy protocol, twice a week

Weeks/goals	Objective	Exercises	Instructions	Progression
First–second	Increase speed of execution from a comfortable speed to a fast speed.	From sitting, get up and walk in an 8-m track, make the turn to the “U” (1 m), and walk diagonally to sit on the next chair.	Get up from the chair and walk to the “U,” go around it and sit on the next chair. Start by performing at comfortable speed, with each command increasing speed (“a little faster”/“fast”/“as fast as you can without running”).	The “U” will decrease (1 m–80 cm pivot), and the height of the chair (50 cm–45 cm–40 cm). Every three repetitions of the circuit will be given the command to increase the speed.

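### Pooling exercise intolerance with falls and injuries leaves the between-arm safety comparison open to differential ascertainment, because the pacing rule differs by arm

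*Protocol article*

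**What the plan says.** Under Primary outcomes, the protocol article states that "Safety will be reported by the number of adverse events" and defines the events: "Adverse events were defined as exercise intolerance, injuries, or falls during the intervention". The three components form one count. The same paragraph sets a criterion for going on to a future trial, "considering < 5% of occurrence of adverse as acceptable". The Background gives the outcome a direction: "We hypothesize that the EMPOWER-PD will lead to higher adherence and safety when compared with conventional physical therapy".

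The arms differ in who sets the pace:

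- **EMPOWER-PD.** Under Interventions groups, "the intensity of the EMPOWER-PD protocol will be self-controlled according to the self-perception of effort of each one". The Empower-PD section adds, for the main part of the session, "being allowed pauses to rest according to the individual’s perception".
- **CPh.** Under Interventions groups, staff control intensity between 55% and 85% of maximum heart rate and prompt participants to walk faster or slower to stay in that range. Table 2 says for weeks 1-2: "Every three repetitions of the circuit will be given the command to increase the speed". It brings the same command back for weeks 7-8. The CPh section also mentions a timer to control circuit speed in some stages.

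Both groups have blood pressure taken before and after each session, and oximeter and Borg monitoring during it. The Randomization section says that blinded testers assess the participants. No section says who records or classifies adverse events in the sessions, or that this person is blinded.

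**The concern.** Falls and injuries do not depend on the pacing rule for their recognition. Exercise intolerance does: it is the inability to sustain a level of effort, and the article gives no criterion for it that is independent of the level requested. A participant who stops from fatigue in EMPOWER-PD is using a permission written into that arm. A participant who stops for the same reason in CPh interrupts work that someone else has set. Staff could reasonably record the two episodes differently, and CPh session staff must know the arm, since they prompt to heart-rate values.

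Safety is a primary outcome, and the trial expects a difference in a stated direction. If the component most open to differing judgement drives the pooled count, a lower total in EMPOWER-PD could be read as a safer programme when part of it comes from how episodes were classified.

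**Working it through.** The plan has no power or precision figure for safety to reproduce. The check is a comparison of passages followed by an illustration.

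**1. The components against the pacing rule**

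| Component | Recognisable without knowing the workload requested? |
|---|---|
| Fall | Yes |
| Injury | Yes |
| Exercise intolerance | Not from the text; no criterion is stated |

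Only the third component is tied to the feature that distinguishes the arms.

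**2. How much one classification can matter**

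The Abstract gives 24 participants allocated 1:1, so 12 per arm. One participant with an event is 1/12 = 8.3% of an arm, above the 5% limit, or 1/24 = 4.2% of the whole sample, below it. The article does not say which denominator applies. If the limit is read by arm and by participant, one judgement about intolerance decides it.

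**3. Illustration of unequal counting**

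Assumptions, none given by the article: each participant has the same true risk q of an intolerance episode in both arms; every episode is counted in CPh; a fraction f is counted in EMPOWER-PD; there are no falls or injuries; participants are independent.

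Counts: CPh ~ Binomial(12, q), EMPOWER-PD ~ Binomial(12, f·q). The chance that EMPOWER-PD looks safer is the sum of P(EMPOWER-PD = i) × P(CPh = j) over all i < j. The chance that it looks less safe is the same sum over i > j. For f = 0 the first reduces to 1 − (1 − q)^12; at q = 10%, 1 − 0.9^12 = 1 − 0.282 = 0.718.

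Each cell shows looks safer / looks less safe:

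| q | f = 1 (one rule) | f = 0.5 | f = 0 |
|---|---|---|---|
| 5% | 0.29 / 0.29 | 0.37 / 0.15 | 0.46 / 0 |
| 10% | 0.36 / 0.36 | 0.52 / 0.18 | 0.72 / 0 |
| 20% | 0.40 / 0.40 | 0.66 / 0.16 | 0.93 / 0 |
| 30% | 0.41 / 0.41 | 0.74 / 0.12 | 0.99 / 0 |

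With one counting rule the two chances are equal. Counting half of the EMPOWER-PD episodes already tilts the comparison clearly.

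**4. The 5% limit by arm**

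Staying below 5% of 12 participants requires zero events. At q = 10% that has probability 0.9^12 = 0.28 in CPh. In EMPOWER-PD it is 0.95^12 = 0.54 with f = 0.5, and 1.00 with f = 0.

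**The case against.** A reader might infer that the safety hypothesis is met by definition: a stop is a permitted rest in one arm and an adverse event in the other. The article does not support this. It states one definition for both arms. It nowhere forbids rest in CPh, labels a CPh stop as intolerance, or exempts an EMPOWER-PD stop from the definition. CPh prompting includes slowing down, and the command to speed up every three repetitions is stated for weeks 1-2 and 7-8, not throughout. Falls and injuries also count. Even the extreme column above (f = 0) gives 0.46 to 0.99, which is not certainty, and that column assumes the unequal counting it illustrates. All of this stands.

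Three further objections carry weight:

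- **Real effect.** Self-chosen intensity is part of EMPOWER-PD. Fewer intolerance episodes under it could be a genuine benefit, which should be reported and not discarded.
- **Condensed article.** The definition cites a source, and a working criterion may exist there or in the full protocol. The absence of one here is therefore not the point. The point is the pooling together with the directional claim, and both are fixed in this text.
- **Descriptive reporting.** Data management and analysis reports safety as numbers, with no between-arm test. This limits the consequence, but the Background hypothesis still invites the comparison.

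The existing monitoring does not settle the matter by itself. The instruments are the same in both arms, but heart rate and perceived effort follow the workload, which differs.

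**Conclusion.** The concern holds as a risk of differential ascertainment in the between-arm comparison of the pooled count. It does not show that the comparison will be biased, or that fewer events in EMPOWER-PD would be an artefact; as planned, the pooled count cannot separate artefact from benefit. The size depends on two unknowns, the episode risk and the share counted in EMPOWER-PD. For risks of 5% to 30% with half counted, the chance that EMPOWER-PD looks safer rises from 0.29-0.41 to 0.37-0.74, and the chance that it looks less safe falls to 0.12-0.18. The conclusion rests on intolerance being judged in sessions by people who are not stated to be blinded, and on no pacing-independent criterion being set elsewhere. If one is set and applied alike in both arms, most of the concern falls away, although separate reporting would still be preferable.

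**What to change.** - Report falls and injuries separately from exercise intolerance, in each arm.
- Rest the between-arm safety statement on falls and injuries.
- Report intolerance as a separate tolerability outcome, under one observable criterion set by the investigators and applied alike in both arms. If the full protocol or the cited source already contains one, state it.
- Log effort-related pauses in both arms as descriptive data. Do not count permitted rests as adverse events: that could simply turn the bias against EMPOWER-PD.
- Do not read a difference in the pooled count alone as a difference in safety.

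The cost is a change of wording, one added line on the session sheet, and sparser counts for each component, which is acceptable in a trial of 24 that reports safety descriptively.
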